**SLAAPDAGBOEK**

| DATUM                   |   | UREN                    |    |    |    |                        |   |   |   |                        |   |   |   |                             |   |    |    |    |    |    |    |    |    |    |    |
|-------------------------|---|-------------------------|----|----|----|------------------------|---|---|---|------------------------|---|---|---|-----------------------------|---|----|----|----|----|----|----|----|----|----|----|
| Week van ... tot ...    | * | **                      |    |    |    |                        |   |   |   |                        |   |   |   |                             |   |    |    |    |    |    |    |    |    |    |    |
|                         |   | 20                      | 21 | 22 | 23 | 24                     | 1 | 2 | 3 | 4                      | 5 | 6 | 7 | 8                           | 9 | 10 | 11 | 12 | 13 | 14 | 15 | 16 | 17 | 18 | 19 |
| Maandag* - Dinsdag**    |   |                         |    |    |    |                        |   |   |   |                        |   |   |   |                             |   |    |    |    |    |    |    |    |    |    |    |
|                         |   | Slapenkwaliteit: .../10 |    |    |    | Waakwakeliteit: .../10 |   |   |   | Gevoel overdag: .../10 |   |   |   | Behandeling en opmerkingen: |   |    |    |    |    |    |    |    |    |    |    |
| Dinsdag* - Woensdag**   |   |                         |    |    |    |                        |   |   |   |                        |   |   |   |                             |   |    |    |    |    |    |    |    |    |    |    |
|                         |   | Slapenkwaliteit: .../10 |    |    |    | Waakwakeliteit: .../10 |   |   |   | Gevoel overdag: .../10 |   |   |   | Behandeling en opmerkingen: |   |    |    |    |    |    |    |    |    |    |    |
| Woensdag* - Donderdag** |   |                         |    |    |    |                        |   |   |   |                        |   |   |   |                             |   |    |    |    |    |    |    |    |    |    |    |
|                         |   | Slapenkwaliteit: .../10 |    |    |    | Waakwakeliteit: .../10 |   |   |   | Gevoel overdag: .../10 |   |   |   | Behandeling en opmerkingen: |   |    |    |    |    |    |    |    |    |    |    |
| Donderdag* - Vrijdag**  |   |                         |    |    |    |                        |   |   |   |                        |   |   |   |                             |   |    |    |    |    |    |    |    |    |    |    |
|                         |   | Slapenkwaliteit: .../10 |    |    |    | Waakwakeliteit: .../10 |   |   |   | Gevoel overdag: .../10 |   |   |   | Behandeling en opmerkingen: |   |    |    |    |    |    |    |    |    |    |    |
| Vrijdag* - Zaterdag**   |   |                         |    |    |    |                        |   |   |   |                        |   |   |   |                             |   |    |    |    |    |    |    |    |    |    |    |
|                         |   | Slapenkwaliteit: .../10 |    |    |    | Waakwakeliteit: .../10 |   |   |   | Gevoel overdag: .../10 |   |   |   | Behandeling en opmerkingen: |   |    |    |    |    |    |    |    |    |    |    |
| Zaterdag* - Zondag**    |   |                         |    |    |    |                        |   |   |   |                        |   |   |   |                             |   |    |    |    |    |    |    |    |    |    |    |
|                         |   | Slapenkwaliteit: .../10 |    |    |    | Waakwakeliteit: .../10 |   |   |   | Gevoel overdag: .../10 |   |   |   | Behandeling en opmerkingen: |   |    |    |    |    |    |    |    |    |    |    |
| Zondag* - Maandag**     |   |                         |    |    |    |                        |   |   |   |                        |   |   |   |                             |   |    |    |    |    |    |    |    |    |    |    |
|                         |   | Slapenkwaliteit: .../10 |    |    |    | Waakwakeliteit: .../10 |   |   |   | Gevoel overdag: .../10 |   |   |   | Behandeling en opmerkingen: |   |    |    |    |    |    |    |    |    |    |    |

▼ Uur van naar bed gaan    A: Alcohol    C: Caffeïne    F: Fysieke activiteit

▲ Uur van opstaan        M: Medicatie    R: Roken

Slaap of dutje

R R R R "Halve" slaap

W W W W Wakker

S S S S Slaperigheid

V V V V Vermoeidheid

Figure 3. Example of a blank sleep diary.

In short, the sleep diary enabled participants to visualize their bedtime, wake-up time, and any nocturnal awakenings. The use of colored squares visualizes periods of sleep, with blank squares indicating wakefulness. Additionally, participants can use the diary to monitor factors that may impact sleep, such as alcohol consumption, medication, caffeine intake, smoking, and physical activity. The diary also includes sections to track the perceived quality of sleep and daytime well-being. The following instructions regarding the use of the sleep diary were provided:

- Complete the items from the previous night in the sleep diary about 20 to 30 minutes after waking up:
  - When you turn off the light to go to sleep, put a mark (downward arrow) to indicate the time of lights off.
  - When you turn on the light to get up in the morning, put a mark (upward arrow) to indicate the time of lights on.
  - When you read a book, watch television or do PC work in bed before light of, indicate this with a vertical line
  - Color the 15-minute boxes that you slept during the night
  - Outline other sleep disturbing factors
  - Rate your sleep quality
- Complete the daytime items in the sleep diary in the evening:
  - Use of alcohol, caffeine, medication (plus details), nicotine
  - Indicate when you took a nap.
  - Mark the times you felt sleepy or fatigued.
  - Rate your awakening quality and your mood
- General instructions:
  - Place your sleep diary in a visible location to enhance the likelihood of consistently filling it out.
  - Avoid clock monitoring during the night. The sleep diary of an overview of the perceived sleep.

From the sleep diary, sleep efficiency was computed as the ratio of total sleeping time to the total time spent in bed, serving as an indicator for sleep restriction therapy. Sleep efficiency represents a possible mismatch between time spent in bed and total sleep time. This therapy involves limiting the hours spent in bed as closely as possible to the actual hours of sleep (i.e. determining the sleep window). To achieve this, the time in bed was restricted to the mean sleep time of the previous week, as recorded in the sleep diary, which heightened sleep pressure. Consequently, excessive time in bed was addressed, and a mild form of sleep deprivation ensued. Importantly, the sleep window was never reduced below 5 hours per night, and the participant was not allowed to make any changes without consulting the therapist. In the long term, this approach facilitates faster sleep onset, improves sleep continuity, and results in a deeper, higher-quality sleep by stabilizing the circadian rhythm and balancing the production of melatonin and cortisol. Daytime naps were permitted, but their duration was restricted to a maximum of 15 minutes and only allowed if taken before 2 p.m.

Changes in the prescribed, restricted time in bed occurred using the following guidelines:

- Sleep efficiency = 80-85% : sleep window is retained
- Sleep efficiency < 80% : a new sleep window is determined by making the total time in bed equal to the mean total sleep time of the past week (sleep window  $\geq$  5 hours because of safety and health concerns)
- Sleep efficiency > 85% : sleep window is extended by 15 minutes

Together with an efficacy > 85% any use of sleep-related medication was phased out in agreement with the participant and in close collaboration with the general practitioner of the participant.

For participants with high levels of anxiety, an exception was permitted. This allowed them to choose their bedtime freely one night per week to avoid heightened alertness caused by stress arising from sleep restriction therapy.

### *iii. Stimulus control*

Insomniacs often develop habits that negatively impact their sleep patterns. For instance, falling asleep easily on the sofa during a favorite TV show but experiencing wakefulness when moving to bed afterward creates a conditioned association between the bedroom and wakefulness. Stimulus control aims to disrupt these conditioning patterns by reestablishing the connection between the bed/bedroom and sleep. The bedroom should be exclusively for sleeping and intimacy, while other activities like working, watching TV, and reading should occur in a different room. Participants were also encouraged to allocate an hour before bedtime for relaxing activities, linking relaxation with the bedroom and promoting healthy sleep conditioning. Additionally, participants were advised to only go to bed when feeling sleepy to enhance the likelihood of a swift onset of sleep and reduce the chances of rumination and worry. Specific instructions provided to participants included:

- Retire to bed only when you feel sleepy.
- If unable to fall asleep within 15 minutes, rise from bed.
- Reserve your bed solely for sleep and intimacy.
- Avoid daytime napping.
- Maintain a consistent sleep-wake schedule.

### *iv. Sleep hygiene*

Sleep hygiene covers advice on lifestyle (e.g., physical activity, diet, substance use) and environmental factors (e.g., temperature, noise, light). Though not typically the primary cause of chronic insomnia, these factors may contribute to ongoing sleep issues. Educating patients about these factors' relative risks aids treatment progress. The goal of sleep hygiene instructions was to address unfavorable sleep behaviors by providing information to enhance sleep quality. Several sleep hygiene instructions are given to patients, some of which align with time-in-bed restriction and stimulus control components:

- Refrain from consuming caffeine 4 to 6 hours before bedtime.
- Avoid smoking before bedtime or during nighttime awakenings.
- Steer clear of alcohol consumption 4 to 6 hours before bedtime.
- Abstain from heavy meals before going to bed.
- Refrain from intense physical training 2 hours before bedtime.

- Ensure your bedroom is a comfortable environment.
- Avoid extreme temperatures in your bedroom.
- Keep your bedroom both quiet and dark.
- Minimize exposure to active screens 1 hour before bedtime.

Caffeine and nicotine from smoking stimulate the central nervous system, negatively impacting sleep. Alcohol, while initially inducing sleep, results in reduced duration and poorer quality due to withdrawal symptoms. Therefore, using these substances before bedtime was discouraged. Intensive exercise close to bedtime activates the autonomic nervous system, raises body temperature, and delays sleep onset. However, physical activity at other times of the day promotes sleep and reduces stress.

#### v. *Relaxation therapy*

(Hyper)arousal is recognized as a contributing factor to the onset and persistence of insomnia. In turn, disrupted sleep can diminish a person's ability to cope with daily stressors. Relaxation therapy aimed to diminish somatic and/or cognitive arousal and its associated autonomic stress response, indirectly improving both sleep quality and pain. Using an information leaflet, participants were encouraged to practice relaxation techniques before bedtime using a self-management approach. This information leaflet included background information on the link between stress and sleep problems, detailed description of different relaxation techniques (i.e. Jacobson's method, visualization, mindfulness) and a detailed description on how to practice and implement these techniques in daily life.

#### vi. *Cognitive therapy*

The cognitive therapy component of CBTi targeted unrealistic expectations regarding sleep needs and daily functioning, misattributions and misconceptions about the causes of insomnia, distorted perceptions of consequences, and erroneous beliefs about sleep-promoting practices. The primary tool for cognitive therapy involved visualizing and discussing the vicious circle of thoughts, behavior, and emotions related to sleep. For instance, a participant might believe that 8 hours of sleep is the optimal amount (thought), leading to anxiety or anger when unable to achieve this goal (emotion). This, in turn, results in counting hours left to sleep and worrying about daytime effects (behavior), fostering mental activity and reducing chances of falling asleep. Participants were assigned a home exercise to identify thoughts related to going to bed, being awake at night, and daytime effects. Subsequently, the therapist challenged these thoughts and explored alternatives with the participant. Importantly, thoughts were not minimized. Three examples are provided in table 5.

##### **Example 1.**

Dysfunctional cognition: "I feel that my insomnia is the result of my age"

Underlying belief: "There is nothing I can do to fix this problem, as I cannot change my age."

Cognitive error: Wrong assumption, wrong identification of the cause.

Intervention/Alternative interpretation: "Do all people of your age encounter the same sleep problems?" – "Apart from some normal changes in sleep structure, not all people of older age suffer from sleep problems. There are always psychological and behavioral factors linked to chronic insomnia, which are actually factors we can control and alter."

##### **Example 2.**

Dysfunctional cognition: "After a night of bad sleep, I am unable to function during the day."

Underlying belief: "Sleep deprivation is detrimental for daytime functioning."

Cognitive error: Exaggeration, generalization.

Intervention/Alternative interpretation: "Did you exclusively experience negative effects and moments on the day(s) following a night of poor sleep?" - "Do the negative effects consistently manifest with the same intensity?" - "Are there potentially other factors contributing to these effects?"

##### **Example 3.**

Dysfunctional cognition: "My partner falls asleep one minute after going to bed, I need to be able to do the same."

Underlying belief: "Everyone has to sleep identically."

Cognitive error: Generalization, absolute and universal thinking.

|                                                                                                                                                                                                                                                                                                                                                                                                                  |
|------------------------------------------------------------------------------------------------------------------------------------------------------------------------------------------------------------------------------------------------------------------------------------------------------------------------------------------------------------------------------------------------------------------|
| 
Intervention/Alternative interpretation: "Do all individuals share the same height and weight?"
 
- "Within certain normal boundaries, there exists significant variability among individuals regarding sleep onset latency, number of awakenings, sleep quality, and duration." - "It is advisable to refrain from social comparisons, as there will always be someone who sleeps better than you."
 |
|------------------------------------------------------------------------------------------------------------------------------------------------------------------------------------------------------------------------------------------------------------------------------------------------------------------------------------------------------------------------------------------------------------------|

Table 5. Examples of maladaptive attitudes and beliefs regarding sleep and their alternatives

vii. *Evaluation and relapse prevention*

During the final CBTi session, the therapy was evaluated, and relapse prevention strategies were discussed. The evaluation involved reviewing apriori defined sleep-related goals and assessing the progress made toward achieving them. The patient's achievements were highlighted to motivate them to continue applying the same sleep principles post-therapy.

Relapse prevention aimed to help participants distinguish between an occasional bad night (acute insomnia) and a genuine relapse (chronic insomnia). Discussions covered potential risk factors, situations, and the role of the social network in assisting participants. The sleep diary was emphasized as a self-management tool for ongoing monitoring and intervention when signs of relapse appeared. Additionally, participants were provided with an informational leaflet summarizing key aspects of CBTi, including sleep education, the sleep diary, scoring system, sleep restriction therapy, stimulus control, sleep hygiene, and cognitive therapy. This resource served as a reference for participants to revisit and reinforce certain aspects as needed.

### Statistical analysis plan

1. **Data source:** Data are derived from nCSP patients with insomnia who participate in this randomised controlled trial. They were evaluated at baseline, at post-intervention and at 3, 6 and 12 months follow-up. The primary outcome is average pain intensity in the last 24h assessed with the BPI.
2. **Analysis objectives:** To investigate the effectiveness of CBTi-BEPM versus BEPM in terms of the above-mentioned primary outcome at 12 months follow-up, and pain-related, sleep related and other secondary exploratory outcomes.
3. **Population:** nCSP patients with insomnia
4. **Endpoints:** Change in outcome measures from baseline to each follow-up point
5. **Covariates:** Sensitivity analyses performed for the primary outcome and all exploratory outcomes by controlling for baseline levels of pain intensity for pain-related outcomes and baseline levels of insomnia severity for sleep-related outcomes. These baseline levels were added to the random-intercept fixed slope linear mixed model analysis as confounding factor.
6. **Handling of missing data:** Analyses are carried out using linear mixed models which can handle missing data.
7. **Statistical methodology:**  
Descriptive statistics were used to report the demographic variables and baseline characteristics of the participating nCSP patients per intervention group, with means (Standard Deviation [SD], range and Inter Quartile Range [IQR]) for continuous variables and frequency (%) for categorical variables. All analyses were by intention-to-treat, with all participants included in the analysis according to their randomly allocated treatment. All analyses were performed in SPSS 24.0. For average pain intensity (primary outcome) and for all explorative, secondary outcomes, the change between baseline and other time points was calculated:  $\Delta 1 = \text{baseline (T0)} - \text{post-treatment (T1)}$ ;  $\Delta 2 = \text{T0} - \text{3-month follow-up (T2)}$ ;  $\Delta 3 = \text{T0} - \text{6-month follow-up (T3)}$ ; and  $\Delta 4 = \text{T0} - \text{12-month follow-up (T4)}$ . Differences in the change in average pain intensity at 12-month follow-up (primary outcome at primary endpoint) and at the other time points (immediately post-intervention, and at 3- and 6-month follow-up) were analysed using a random-intercept fixed slope linear mixed model (incl. LSD post-hoc analyses), which was applied using an unstructured covariance matrix. Linear mixed models are a likelihood-based estimation procedure whereby likely values for missing data are estimated from information contained in the observed data, resulting in non-biased estimates providing data are missing at random. The model included treatment, time, and treatment\*time as fixed effects together with a random intercept for each patient. Model assumptions were evaluated visually using residual plots. Mean group differences (95% confidence interval) at the different time points and their p-values and effect sizes for the intervention comparisons are reported. Level of significance for the primary outcome was set at  $\alpha .05$ . Effect sizes were calculated as Cohen's d (interpreted as  $>1.3$  = very large;  $.80-1.29$  = large,  $.50-.79$  = medium,  $.20-.49$  = small,  $<.20$

= negligible). The same analysis was used to evaluate the explorative, secondary outcomes at the different time points.

Sensitivity analyses were performed using the same analysis, including the baseline level of average pain intensity (for all pain-related outcomes) and the baseline level of insomnia severity (for sleep-related outcomes) as confounding factor. The analysis of dropout and loss-to-follow-up was conducted by categorizing the entire cohort into two subsets, distinguished by their adherence or discontinuation from the trial (which also included loss-to-follow-up). Comparative assessment of baseline characteristics and data between the two groups was accomplished utilizing a t-test or its non-parametric equivalent.

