**Sample size calculation:**

Sample size (n=120) is calculated using G\*Power based on the effects on pain in a pilot study (Cohen's  $f = 0.25$ ,  $\alpha = .05$ ,  $\text{power} = .80$ ), accounted for F-tests and 20% loss to follow-up after one year.

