**Randomisation:**

Randomization is computer-generated at the Biostatistics Unit of Ghent University by an independent investigator, uninvolved in any other trial aspects. Block randomisation was used (ratio 1:1) for the two treatment centres (Ghent; Brussels) separately, with stratification for sex (male; female) and dominant pain location (neck; low back). The randomisation is performed by an independent researcher, who places papers indicating group assignment in sequentially numbered, opaque, and sealed envelopes. Concealed allocation is ensured since the independent researcher – who will be the only person with access to the envelopes – writes the initials of the selected participants on the appropriate envelope before opening them.

**Outcome measures:**Primary outcome:

The primary clinical outcome is defined as average pain intensity, assessed using the Brief Pain Inventory (BPI) item 'average pain intensity in the last 24h' evaluated on an 11-point NRS (30% decrease is clinically important).

Explorative, secondary pain-related outcomes:

- BPI worst pain intensity (last 24h) on an 11-point (0–10) numeric rating scale
- BPI least pain intensity (last 24h) on an 11-point (0–10) numeric rating scale
- BPI pain intensity now on an 11-point (0–10) numeric rating scale
- BPI pain severity: the mean of the four pain intensity items
- BPI pain interference: the BPI also evaluates the pain interference related to general activity, walking, work, mood, enjoyment of life, relation with others and sleep on separate 11-point numeric rating scales.
- The Central Sensitisation Inventory (CSI; cut-off value of 40/100 to indicate the presence of central sensitization-related symptoms) to assess symptoms of central sensitisation. The CSI uses 25 statements related to current health symptoms, indicative of central sensitization (scored on a five-point Likert scale ranging from zero to four).

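### The intention-to-treat statement does not fit the likely change-score primary model, and the pooled dropout check and missing-at-random analyses protect little against arm-related dropout

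*Combined protocol and SAP*

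**What the plan says.** Item 7 of the Statistical analysis plan describes the analysed set: "All analyses were by intention-to-treat, with all participants included in the analysis according to their randomly allocated treatment". Item 3 gives the population only as patients with the condition under study, so no other text defines who is analysed.

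Item 4 gives the endpoint as "Change in outcome measures from baseline to each follow-up point". Item 7 computes four differences, T0 minus T1, T2, T3 and T4, and names the quantity compared: "Differences in the change in average pain intensity at 12-month follow-up (primary outcome at primary endpoint". The primary mixed model has treatment, time, their interaction and a patient-level random intercept. Baseline pain enters only in the sensitivity analysis (item 5 and the end of item 7).

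Missing data are left to the likelihood, described as "resulting in non-biased estimates providing data are missing at random". The one dropout analysis works by "categorizing the entire cohort into two subsets, distinguished by their adherence or discontinuation from the trial", with loss to follow-up counted as discontinuation, and compares baseline data by t-test or a non-parametric equivalent. No dropout comparison by arm, and no analysis under a different missing-data assumption, is specified.

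The Sample size section sets n = 120 and says it is "accounted for F-tests and 20% loss to follow-up after one year".

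**The concern.** A mixed model keeps a patient who has at least one response row. If the response is the change score, a patient seen only at baseline has no row, and the likelihood has nothing to work with. That contradicts the statement that everyone is included. It also discards the baseline scores that would let the model correct for dropout related to baseline pain.

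The dropout check does not fill the gap. What biases a treatment contrast is dropout related to outcome in a way that differs between arms, and a comparison of leavers with stayers across both arms together is not aimed at that. The difference could matter here, because the Interventions section gives time-in-bed restriction to the CBTi-BEPM arm only, so reasons for leaving could differ by arm. At stake is whether the 12-month pain result can be trusted if losses approach the planned level.

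**Working it through.** **Inputs from the documents.** n = 120, allocation 1:1 (60 per arm), Cohen's f = 0.25, alpha 0.05, power 0.80, 20% loss at one year.

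**The plan's own figure.** A repeated-measures F-test between two groups, with two measurements and within-person correlation 0.5, needs 98 patients. Inflating gives 98/0.8 = 122.5, so 123, or 98 × 1.2 = 117.6, so 118. Conversely, 120 × 0.8 = 96 completers give power 0.799. So 120 can be reproduced approximately, but the number of measurements and the correlation are not in the documents. The point below needs only the planned loss: 120 × 0.2 = 24.

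**Who is left out of a change-score model.** Only patients lost before any follow-up score have no row. Taking loss before T1 as that case:

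| Share of the 24 losses before T1 | No row | In the model |
|---|---|---|
| 0% | 0 | 120 |
| 25% | 6 | 114 |
| 50% | 12 | 108 |
| 75% | 18 | 102 |
| 100% | 24 | 96 |

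The documents do not say when losses are expected, so the range stays 0 to 24.

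**Bias and detection by dropout pattern.** Simulation assumptions, none from the documents: SD 2, correlation 0.5, no true effect, about 20% dropout overall, log-odds of dropout 1 per SD. Detection is at the 5% level with 60 per arm. Bias is the absolute error in the 12-month difference, in NRS points. Where two values are separated by a slash, they are for loss before and after T1.

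| Dropout pattern | Bias, change score | Bias, T0 as a response or baseline as covariate | Pooled check flags | Arm-by-dropout test on baseline flags |
|---|---|---|---|---|
| Baseline-related, opposite directions by arm | 0.36 / 0.18 | about 0 | 6.8% | 97.5% |
| Baseline-related, one arm only | 0.18 / 0.09 | about 0 | 50% | 47% |
| Baseline-related, same direction in both | about 0 | about 0 | 97% | 4% |
| Completely random, 10% v 30% | about 0 | about 0 | 5% | 5% |
| Depends on unseen T4 pain, one arm | 0.19 | 0.25 to 0.28 | 16% | 17% |
| Depends on unseen T4 pain, opposite directions | 0.36 | 0.48 to 0.55 | 5% | 48% |

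The pooled check is near its 5% error rate in the first row, where the primary estimate is biased, and flags 97% in the third, where it is not. Using baseline removes bias in the first two rows but not in the last two. In the fifth row, splitting the baseline comparison by arm gains almost nothing.

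**Sensitivity to missing at random.** Suppose missing CBTi-BEPM pain scores at T4 are delta points worse than the model predicts.

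- Shift in effect = fraction missing × delta: 0.2 × 1 = 0.2; 0.2 × 2 = 0.4.
- Standard error = SD × √(2/48), with 48 observed per arm (60 × 0.8). For SD 1.5, 2 and 2.5 it is 0.31, 0.41 and 0.51.
- Movement in z for delta 1: 0.65, 0.49 and 0.39. For delta 2, twice that: about 1.3, 1.0 and 0.8.

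For two groups f = 0.25 is d = 2 × 0.25 = 0.5, which is 0.5 × 2 = 1.0 NRS point at SD 2. The shift is then 20% to 40% of the effect the trial was sized for.

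**The case against.** The text never says outright that the model's response is the difference. Treatment, time and interaction terms would also suit raw scores with T0 as a time level, and then everyone with a baseline score is in. This stands as a caveat. The named endpoint, the four computed differences and the use of baseline as an added covariate make the change-score reading the likelier one.

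A reader might infer that the intention-to-treat sentence is simply untrue, or that a fifth of the trial is excluded. The documents support neither. Patients lost after T1 remain, and analysis by allocated arm is unaffected.

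The plan does include a baseline-adjusted sensitivity analysis, which removes bias from baseline-related dropout in the simulation. That stands too. It is secondary, however, does not bring back patients without a follow-up score, and still assumes missing at random.

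A reader might also infer that the pooled check can never reveal harmful dropout. It can: it flagged one-arm, baseline-related dropout in about half of simulated trials. Nor should the argument rest on the trial being open, since the Design section calls it triple-blind.

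Finally, a likelihood analysis under missing at random is a legitimate primary approach, and the SAP states the assumption. Agreed; what is missing is any test of how far the conclusion depends on it.

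**Conclusion.** The point holds in a conditional form. If the response is the change score, as the SAP most likely means, then between 0 and 24 of 120 patients under the planning loss would contribute nothing, contrary to the stated analysed set. The unadjusted primary estimate is then open to bias from baseline-related dropout that differs by arm: about 0.1 to 0.4 NRS points in the simulated patterns. Whichever response is meant, the dropout check is weak against opposite-direction dropout, and no planned analysis departs from missing at random.

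The 20% is a planning allowance, not an observed loss. The SD, correlation, dropout strength and delta are assumptions. The figures therefore show how sensitive the result could be. They do not show that it is biased, or that dropout will differ by arm. The change is worth making because it is cheap and concerns the primary estimate. The by-arm dropout table alone would be a reporting detail.

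**What to change.** 1. Make the primary analysis a constrained-baseline mixed model: T0 to T4 pain as responses, a common mean at T0, and the treatment difference at T4 as the primary contrast. Say explicitly that raw scores are modelled and that the analysed set is every randomised patient with a baseline score. This costs SAP wording and uses data already collected. It does not cure bias from dropout that depends on unseen pain; in the simulated patterns of that kind its bias was somewhat larger than the change-score model's.
2. Add a delta-adjusted tipping-point analysis for T4 pain. For example, shift imputed CBTi-BEPM values by 0 to +2 NRS points and report the delta at which the conclusion changes. This costs one multiple-imputation run.
3. As supporting reporting, give dropout counts, reasons and baseline pain by arm, rather than the pooled comparison alone. This needs no new outcome data, only that reasons for leaving are tabulated by arm where recorded.
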